#### · *Perceived knowledge*

Participants’ perceived knowledge of sarcopenia prevention will be assessed by using true or false questions. The 21 questions reflect the main points of the seven topics in the sarcopenia prevention health education strategy. Final evaluation of the participants’ mastery of health education knowledge will be based on the proportion of correct responses. These sarcopenia quizzes were developed in our previous study [23], which involved a literature search, followed by two rounds of PPI consultations (eight older adults, four sarcopenia and health education experts) and two rounds of focus group interviews (31 older adults with possible sarcopenia). All these stakeholders reviewed and approved the content of the questions which lends itself to content validity.

#### · *Personal motivation*

Self-Efficacy for Managing Chronic Disease 6-item Scale (SEMCD-6) developed by the Stanford Patient Education Research Centre in a Chronic Disease Self-Management Program will be used to identify and measure the confidence level of older adults in adopting appropriate behavioral skills to prevent and manage chronic disease [43,44]. Scores on this scale are calculated as the means of the six items, including self-efficacy to manage symptoms (4 items) and self-efficacy to manage disease (2 items), each measured on Likert scales ranging from 1 (not at all confident) to 10 (totally confident). The higher the score, the greater the participant’s confidence in completing the disease management mission. Measures of SEMCD-6 reliability have been found to be high (= 0.91), and test-retest reliability has been reported to be statistically significant (r = 0.87).

#### · *Behavioral skills*

Self-management Behavior for Chronic Disease Scale also developed by the Stanford Patient Education Research Centre will be used to identify and measure older adults’ actual behavioral skills in daily life for preventing and managing chronic disease [43–45]. The scale includes exercise management (5 items), cognitive symptom management (6 items) and communication with physicians (3 items). Exercise management is measured by examining the total time spent engaging in physical activities, such as stretching and strengthening exercises, walking, swimming, bicycling, and aerobics (categorized respectively as 0: none, 1:<30min/ week, 2: 30-60min/week, 3: 1-3h, or 4: >3h/week). Cognitive symptom management is measured on a 6-point Likert scale, ranging from never to always, and includes distraction, progressive muscle relaxation, imagery, positive thinking, and self- distance. Communication with physicians is measured as the number of times the participants prepared a list, asked questions, and discussed problems with the provider on a 6-point Likert scale ranging from never to always.

#### · *Behavior change monitoring*

Three aspects of behavior change will be monitored throughout the entire research procedure, including: 1) Exercise adherence during the intervention and follow-up periods will be calculated by completion rate of minimum exercise required in the study. The Exercise Adherence Rating Scale (EARS) is a validated 16-question instrument with a 6-question subscale assessing adherence; the remaining questions measure reasons for adherence/non-adherence. As stated in the study [46], EARS is a valid and reliable tool that allows for the assessment of compliance with suggested home exercise. The six items comprise a unidimensional scale that exhibited favorable measurement features, including satisfactory internal consistency and strong test-retest reliability. 2) Percentage of participants who actively view and share sarcopenia-related information to others. 3) Percentage of participants willing to formulate habits of regular exercise to prevent sarcopenia at the end of the current study. 4) Exposure percentage of exercise and sarcopenia-related videos = Number of exercise and sarcopenia related videos viewed / Twenty videos. TikTok can push videos to users that they are interested in based on big data algorithms; therefore, if participants begin to view more videos about exercises and sarcopenia after health education in our research, TikTok will capture these changes in their viewing habits and push more videos about exercises and sarcopenia to them. Then, researchers can record the number of exercise and sarcopenia-related videos when every twenty videos are viewed on participants’ TikTok and observe the exposure percentage of exercise and sarcopenia-related videos to determine if participants’ video-scrolling behavior changes.

#### · *Social-demographic information*

The participants will respond to single-item questions regarding their age in years, gender, long-term condition, medication, level of education, and any significant health issues that may impact their ability to engage in physical activity, as well as whether they use a mobility aid.

#### · *Qualitative Interview*

After the six-week follow-up period, all participants, including those who withdraw at any point, will be offered a semi-structured interview in an office provided by the community health center to assess their experiences with the intervention and research process. This will take about 30min. Family members/ caregivers may also be invited to the interview at the request of the participant.

### Timeline

This will be a 17-week study, including 2-week recruitment, 1-week health education, 6-week exercise intervention, 6-week follow up, and 2-week interview. The expected completion date for the research is between May 2024 and September 2024. The recruitment phase will last approximately ten days because, during the intervention development phase, our research group collaborated with medical personnel at community health service centers and gained experience in recruitment. Fig 1 illustrates the comprehensive research procedure and precise timetable.

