Therefore, our research team co-created a Social-media based Health Education plus Exercise Program (SHEEP) for preventing possible sarcopenia through behavior change in community-dwelling young-old adults. Full details of the development study are published elsewhere [3,23]. In brief, we constructed a SHEEP Conceptual Model primarily guided by the Behavior Change Wheel (BCW) [24] and the conceptual model for Lifestyle-integrated Functional Exercise using smartphones and smartwatches (eLiFE) [25], with the objective of developing intervention content and the monitoring process. Then, we co-designed a multicomponent social media-based (TikTok) intervention based on the SHEEP Conceptual Model. After a three-week preliminary test, the results from semi-structured interviews indicated that the participants complied well with the SHEEP intervention and provided positive feedback for both health education and exercise components. Not only did participants subjectively report that their grip and leg strength increased after exercise, they perceived that their mood, sleep, and diet also improved. Simultaneously, participants reported that the program positively altered their attitudes and behaviors toward sarcopenia prevention, and that they would continue to exercise after the study was completed. They were also willing to recommend the program to others. To ensure a more impartial assessment of the potential impact of SHEEP intervention on the intended population, we devised this extended feasibility study prior to proceeding with a prospective RCT.

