#### · *Exclusion criteria*

Unable to communicate or independently complete learning and exercise using TikTokSerious or unstable medical illness, such as severe cardiovascular or respiratory conditions, mental disorder, dementia, etc.Currently undertaking regular exercise (e.g. Tai Chi and Square Dance) and exercise intensity is moderate (≥ 150mins/week)Contraindications for the use of Bioelectrical Impedance Analysis (BIA), such as people with implanted cardiac pacemakers, or other electronic devices or metal grafts, or with significant pitting oedema, or with limb dysfunction or body paralysis, or while taking medications that affect body composition, such as diuretics or glucocorticoids.

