### Sample size

One arm of 35 eligible participants will be recruited. A sample size of 30 participants after attrition (attrition rate 10%~15%) is normally used for a feasibility study [33,34]. Convenience sampling will be utilized in this research. The target population in the two communities will be divided into four categories based on age (60–65 and 66–69 years) and gender (male and female), to determine if there are differences in the acceptability of the intervention process among subgroups of individuals.

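### People who co-designed or pre-tested SHEEP are neither excluded nor identifiable, so carry-over of unknown size could affect adherence, acceptability and baseline knowledge

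*Protocol article*

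**What the plan says.** **Who was exposed earlier.** The section on perceived knowledge says that the quiz came out of a literature search and work with stakeholders, among them "two rounds of focus group interviews (31 older adults with possible sarcopenia"). Eight older PPI members and four experts were consulted as well, and every one of these groups checked and endorsed the items. The Introduction describes people who tried the programme itself: "After a three-week preliminary test, the results from semi-structured interviews indicated that the participants complied well with the SHEEP intervention". They reported stronger grip and legs, meant to keep exercising and would recommend the programme. Their number is not given.

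**Who can enrol now.** The inclusion and exclusion criteria are itemised in detail, and none concerns earlier SHEEP involvement. The nearest is the exercise exclusion: "Currently undertaking regular exercise (e.g. Tai Chi and Square Dance) and exercise intensity is moderate (≥ 150mins/week"). The social-demographic questions do not ask about earlier involvement.

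**How people are found.** Under Sample size: "Convenience sampling will be utilized in this research". The recruitment section describes paper leaflets for health-centre visitors, electronic leaflets to community WeChat groups, and contact with the PI directly or through the centre managers. The Timeline expects recruitment to take about ten days because "during the intervention development phase, our research group collaborated with medical personnel at community health service centers and gained experience in recruitment".

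**The concern.** An earlier participant has no clean baseline. A quiz reviewer has already seen the items and approved their content. A preliminary tester knows the programme, may still be doing the exercises and has already given favourable feedback.

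The outcomes affected are central to the study. Recruitment rates, adherence and participants' evaluation belong to the primary aim, and willing returners would push them upward. Quiz knowledge is a secondary outcome measured from T0, and a raised T0 score makes the measured gain smaller. The Outcomes section says the data will help choose a primary outcome and supply parameters for the sample size of a later RCT, so a distorted rate or change could be carried forward. Because earlier involvement is not among the listed baseline items, the effect could not be checked afterwards from the data described.

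**Working it through.** **1. The plan's own figure.** The plan states "One arm of 35 eligible participants will be recruited" and "A sample size of 30 participants after attrition (attrition rate 10%~15%) is normally used for a feasibility study". Inflating 30 for attrition d as 30/(1 − d):
- d = 10%: 30/0.90 = 33.3, rounded up to 34
- d = 15%: 30/0.85 = 35.3, rounded up to 36

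The stated 35 lies between these, so the sample size reproduces. The point concerns eligibility and does not change it.

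**2. Size of the exposed group.** The focus-group members alone equal 31/35 = 89% of the target sample. This shows only that the group is not small beside the sample; it does not estimate how many would enrol. The article does not give their age or SARC-CalF score, or say whether they live in these two communities. The number of preliminary testers, and whether they were among the 31, is also not stated.

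**3. Does the exercise exclusion catch them?** The SHEEP minimum is 3 sessions × 30 minutes = 90 minutes a week, below the 150-minute threshold. Someone still following SHEEP at its minimum passes; only at 5 × 30 = 150 minutes would the criterion apply. Someone who only reviewed the quiz is not touched by it at all.

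**4. Illustration.** None of the following values comes from the documents; all are assumptions. Let k of 35 be previously exposed and f = k/35. Assume adherence of 70% in naive and 95% in exposed people, a baseline quiz score of 50% and 75%, and a later quiz score of 85% in both.
- Adherence = 70 + 25f
- Baseline quiz = 50 + 25f
- Quiz gain = 85 − (50 + 25f) = 35 − 25f

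| k | f | Adherence (%) | Baseline quiz (%) | Quiz gain (points) |
|---|---|---|---|---|
| 0 | 0.000 | 70.0 | 50.0 | 35.0 |
| 3 | 0.086 | 72.1 | 52.1 | 32.9 |
| 5 | 0.143 | 73.6 | 53.6 | 31.4 |
| 10 | 0.286 | 77.1 | 57.1 | 27.9 |
| 15 | 0.429 | 80.7 | 60.7 | 24.3 |

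A wider assumed contrast gives similar sizes. With quiz scores of 90% against 60%, the baseline mean rises by 30 × 4/35 = 3.4 to 30 × 10/35 = 8.6 points for k = 4 to 10. With all exposed people adherent against 70% of naive people, adherence reads (4 + 0.7 × 31)/35 = 73% to (10 + 0.7 × 25)/35 = 79%.

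The adherence column should be read as applying to preliminary testers, since the quiz reviewers are not said to have done the exercises. The quiz columns can apply to both groups.

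**The case against.** **Recruitment through earlier contacts.** A reader might infer from the Timeline that recruitment relies on participants known from the development phase. The text does not support this. It names collaboration with medical personnel and experience gained. The recruitment section describes leaflets, WeChat groups and people coming forward themselves; no re-contact and no list of earlier participants is mentioned. Nor does the article say that development took place at the two centres named for this study. This objection stands in full: overlap is possible, not shown.

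**Target population.** A reader might also treat all 31 focus-group members as eligible people who have done SHEEP. They are described only as older adults with possible sarcopenia who reviewed the quiz. This objection stands too, and it is why the 31 cannot serve as a basis for the adherence figures.

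**Impartial assessment.** The Introduction wants a more impartial assessment after the preliminary test. One could read this as a promise of a sample new to SHEEP. It follows a description of subjective interview reports, so the natural contrast is with subjective feedback, and no such promise is made.

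**Size and direction.** For adherence of 70% in 35 people, the approximate 95% half-width is 1.96 × √(0.7 × 0.3/35) = 15 points, so the assumed shifts up to k = 10 lie inside sampling error. On knowledge the bias works against a favourable result. Both remarks are fair and limit the weight of the point. They do not remove it: a bias is not reduced by being smaller than the interval, and a gain that is too small can still mislead the planning of the RCT.

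**Condensed article.** The criteria are listed in such detail that condensation is a weak explanation for a missing item.

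**Conclusion.** The point holds in limited form. As written, the plan can enrol people who co-designed or pre-tested SHEEP, and its listed baseline items would not identify them. Recruitment, adherence and acceptability would tend to be biased upward, mainly by preliminary testers. Baseline quiz scores would be raised by testers and quiz reviewers alike, and the measured knowledge gain lowered.

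The size is unknown, because neither the overlap of sites nor the number who would enrol is stated. The figures in the table show direction and order of magnitude under assumed values and are not estimates. If the earlier work was done elsewhere, the effect may be nil. The change is nonetheless worth making before recruitment, because it is cheap and the omission is hard to repair afterwards.

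**What to change.** Add one exclusion criterion: earlier participation in SHEEP co-design (PPI consultations or focus groups) or in the three-week preliminary test. Ask it at the phone or email pre-screen, which already covers the exclusion criteria. State in the article whether the earlier work used the same two centres.

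If the sponsor prefers to keep such people, record earlier involvement at T0, separating quiz review from use of the programme, and report the primary rates and the knowledge change with and without them.

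The cost is one line and one question. The target stays at 35, and recruitment may be slightly slower. The second option leaves fewer naive people: 5 flagged would leave 35 − 5 = 30 before attrition, where the plan wants 30 after it. Exclusion is therefore the cleaner choice.

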**Fig 1 pone.0303481.g001:**
[figure not shown]
A brief diagram of the feasibility study procedure and timeline.

### Data collection and analysis

The PI, who is qualified and experienced with all of the measurements, will be responsible for data collection. To promote the collection of high-quality data, the PI will double-check the collected data.

As for quantitative data analysis, descriptive statistics will be utilized to summarize the percentage of recruitment, baseline participant characteristics (e.g. age, gender, and educational background), attrition rate, compliance rate, height, weight, etc. 95% confidence intervals (CIs) of mean values will be used to determine the difference of secondary outcomes before and after intervention, such as handgrip strength, skeletal muscle mass, body fat, etc. All statistical analyses will be conducted using SPSS Statistics 27.0 (IBM Corp., Armonk, NY, USA). P Values <0.05 will be interpreted as indicating significance.

Regarding the collection of qualitative data, all face-to-face semi-structured interviews after the follow-up period will be audio recorded using an encrypted digital recorder. If participants prefer a telephone interview, the conversation will be recorded on an encrypted Dictaphone. All encrypted recordings will be uploaded to a secure server at the University of Manchester and then deleted from the recording device. Moreover, each interview will last between 30 minutes and one hour, and participants will only be asked to participate in one. During the data analysis stage, we will analyze the qualitative data using thematic analysis. Qualitative data will be transcribed verbatim and potentially identifying information will be removed. The transcripts will be compared to the original recordings, corrected as needed, and anonymized. To become familiar with the qualitative data, researchers will first read all transcripts. Themes will be developed based on the interview guide and research team discussion to identify the key characteristics of the qualitative data. Then, codes will be generated for each line of each transcript and categorized accordingly. Before finalizing the major themes, each category must be re-evaluated and scrutinized, and groups of major categories will be refined. Two researchers will perform and review the coding process to ensure a double check, followed by a discussion to ensure the validity of the data. To increase the transparency of the interpretation, the Chinese-to-English and English-to-Chinese translation of quotations will be performed in this study. QSR International’s NVivo 12 qualitative analysis software will be used to assist and facilitate the coding and analysis process. We will refer to the theoretical standpoints from the SHEEP Conceptual Model [23], the BCW [24] and the conceptual model for eLiFE [25] when analyzing the qualitative data in this study.

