## Materials and methods

### Study design

A single-arm prospective pre-post study will be conducted to evaluate the feasibility, acceptability, and preliminary impact of the SHEEP on the prevention of possible sarcopenia in community-dwelling young-old adults. In this seven-week intervention with six-week follow-up study, both quantitative and qualitative methods will be employed to evaluate the outcomes. This research protocol was based on the Standard Protocol Items: Recommendations for Interventional Trials—13 (SPIRIT-13) checklists (S1 and S2 Files) and Template for Intervention Description and Replication (TIDieR) checklist (S3 File).

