### Outcomes

As this is a small feasibility study, the main aim is to assess the feasibility and acceptability of the entire research process, from recruitment to the delivery of the intervention and the use of the outcome measurements. The secondary objectives are to compare standard measures at baseline, seven-week post-intervention, and six-week follow-up for muscle-related outcomes, other body measurements as detailed below, and study adherence to evaluate the potential efficacy of the intervention. The outcome measures will be collected at different time points to identify an appropriate primary outcome and estimate parameters for a sample size calculation for an RCT in the future. Final semi-structured interviews with all participants will be conducted to investigate the viability of the intervention and study procedures in greater detail.

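### The only method stated for before-after change is a 95% CI of mean values; read literally, this is not an interval for the within-person change that the pre-post design measures.

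*Protocol article*

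**What the plan says.** The Study design section describes one group followed over time: "A single-arm prospective pre-post study will be conducted to evaluate the feasibility, acceptability, and preliminary impact of the SHEEP". The Outcomes section sets the secondary objective, which is to "compare standard measures at baseline, seven-week post-intervention, and six-week follow-up for muscle-related outcomes" and for other body measurements. Table 1 schedules handgrip, body composition, walking speed, sit-to-stand and the questionnaire scales at T0, T4, T7, T10 and T13 in the same participants.

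The method for these comparisons is one sentence in Data collection and analysis: "95% confidence intervals (CIs) of mean values will be used to determine the difference of secondary outcomes before and after intervention". The same paragraph adds "P Values <0.05 will be interpreted as indicating significance", without naming a test. The article nowhere mentions a mean change per person, a paired test, a repeated-measures model, or a rule on who enters the comparison.

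The Outcomes section gives these results three uses: to judge potential efficacy, to pick a primary outcome for a later trial, and to "estimate parameters for a sample size calculation for an RCT in the future". The Sample size section says "One arm of 35 eligible participants will be recruited" and plans for about 30 to remain.

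**The concern.** In a single-arm pre-post study each participant is their own control. Stable differences between people, which dominate the spread of measures such as grip strength or muscle mass, cancel when each person's later value is subtracted from their own baseline. The CI of a mean keeps that spread in. Used to judge a before-after difference, it is an error bar for a different quantity, and usually a wider one.

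Three things are at stake. An outcome that responds may look unresponsive and be passed over when the later trial's primary outcome is chosen. The SD of change and the baseline to follow-up correlation, which are useful if that trial analyses change or adjusts for baseline, are not among the planned results. And if the baseline mean and a later mean rest on different people, their difference contains who left as well as who changed.

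**Working it through.** **Plan's own figure.** The Sample size section states: "A sample size of 30 participants after attrition (attrition rate 10%~15%) is normally used for a feasibility study". Inflating 30 for attrition gives 30/0.90 = 33.3, so 34, and 30/0.85 = 35.3, so 36. The planned 35 lies between them, and 1 − 30/35 = 14.3% is inside the stated range. The 35 does not come from a power calculation, so nothing below alters it.

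**Inputs.** From the article: n = 30 completers and 95% intervals. Assumed, because the article gives no values: equal SD at both visits (results are in units of that SD) and a within-person correlation r of 0.5 to 0.9.

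**Half-width of the 95% interval for a before-after difference, n = 30.**

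- Paired change: t(0.975, 29) × √(2(1 − r)/30), with t = 2.045.
- Two means treated as independent: t(0.975, 58) × √(2/30) = 2.002 × 0.258 = 0.52 SD, whatever r is.

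| r (assumed) | Paired, SD | Unpaired, SD | Unpaired / paired |
|---|---|---|---|
| 0.5 | 0.37 | 0.52 | 1.4 |
| 0.7 | 0.29 | 0.52 | 1.8 |
| 0.8 | 0.24 | 0.52 | 2.2 |
| 0.9 | 0.17 | 0.52 | 3.1 |

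**What this does to detection.** For an illustrative true change of 0.3 SD (not a figure from the article), the paired analysis excludes zero with probability 36%, 54%, 71% and 94% at r = 0.5, 0.7, 0.8 and 0.9. The unpaired comparison does so with probability of about 12%, 6%, 3% and 0.4%. With no true change, the unpaired comparison declares a difference about 0.5% of the time or less, against a nominal 5%. It errs towards missing change, not towards claiming it.

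**If separate intervals were compared by overlap.** Two 95% CIs of means stop overlapping at a gap of 2 × 2.045/√30 = 0.75 SD. The article does not state this rule; the figure only bounds the least efficient reading.

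**Dropout, if each mean used whoever was measured.** Suppose 35 are measured at baseline and 30 later, nobody changes, and the 5 lost were k SD lower at baseline. The mean then rises by (5/35) × k. For k = 0.25, 0.5 and 1.0 (assumed) that is 0.036, 0.071 and 0.143 SD, or 21%, 43% and 86% of the paired half-width at r = 0.9, and 15%, 30% and 60% at r = 0.8.

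**The case against.** The strongest reply is that the sentence is loose English for the CI of the mean difference. It speaks of determining a difference, and it does not say that an interval will be formed separately at each visit. The significance threshold in the same paragraph implies that some test is intended, and comparing intervals by eye yields no P value. This stands as a real possibility. It does not remove the point, because nothing in the article settles the reading and two analysts could follow the sentence differently. If the paired interval was meant, the same edit resolves it.

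A second reply is that the analysis set and missing-data handling are commonly left to a fuller document that is not shown. That also stands, so the dropout shift can be raised only as a possible consequence.

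A third is that the Outcomes section does not ask for the SD of change or the correlation by name. The Randomization section says a cluster trial is planned, and a calculation on follow-up values could use the ordinary SD. Nothing stops the team from computing the correlation from the data in Table 1. This is fair: those quantities are useful but not strictly required.

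Finally, the main aim is feasibility and acceptability, the affected outcomes are secondary, and ignoring the pairing is conservative. This limits the severity.

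**Conclusion.** The point holds at moderate severity. The one stated method does not, as written, give an interval for within-person change, and nothing else in the article restores the pairing. If the two means are treated as independent, the interval is 1.4 to 3.1 times as wide as the paired one at n = 30. This assumes equal SDs and correlations of 0.5 to 0.9, which are not in the article.

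Three stronger conclusions that a reader might draw are not supported:

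- That the plan judges change by non-overlap of separate intervals and so needs a change 2.6 to 4.5 times as large as a paired analysis at r = 0.7 to 0.9 (0.75 SD against 0.29 to 0.17 SD). No such rule is stated.
- That dropout will be mixed into the estimates. The analysis set is not given, so this is a possibility under the planned attrition.
- That changes of the expected size would be missed. The article gives no expected change for any secondary outcome.

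The feasibility aim and the sample of 35 are unaffected.

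**What to change.** Replace the sentence on confidence intervals in Data collection and analysis with wording to this effect:

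> For each continuous secondary outcome, the mean within-person change from T0 to T7 and from T0 to T13 will be reported with its paired 95% CI, the SD of change, the baseline to follow-up correlation and the number analysed, among people measured at both times (or from a linear mixed model with time as a factor using all visits).

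This settles the reading, ties the interval to the quantity of interest, makes the set of people behind each estimate explicit and supplies parameters for the later trial. It costs analysis wording only: no new data, visits or participants, and both approaches run in SPSS 27.
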